# STATISTICS AND ANALYSIS

## Description of Statistical Methods

The primary statistical analysis of efficacy outcomes will be carried out on the basis of intention-to-treat (ITT). We will endeavour to obtain full follow-up data on every participant to allow full ITT analysis, but we will inevitably experience the problem of missing data due to withdrawal, loss to follow up, or non-response to questionnaire items.

We will analyse the primary and secondary outcomes with a linear regression model with adjustment for practice and baseline values. We will assess the sensitivity of the analysis to different assumptions about missing data using two imputation methods commonly used: completer only analysis and baseline observation carried forward.

The results from the trial will be prepared as comparative summary statistics (difference in means) with 95% confidence intervals. All the tests will be done at a 5% two-sided significance level. The study results will be reported in accordance with the CONSORT (Consolidated Standards of Reporting Trials) 2010 statements. A full detailed analysis plan (including plans for any interim analysis, subgroup analysis, and sensitivity analysis) will be prepared and finalised before any data analysis.

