## The Number of Participants

The total number of participants we intend to recruit for this study is 112, with a sampling ratio of 1:3:3. Therefore, 16 participants will be allocated to control, and 48 participants will be allocated to each of the two active interventions.

Previous studies such as highly controlled interventions in populations with high CVD risk have achieved absolute changes in %SFA intakes of around 4-5%^6 7^, and a short-term change in LDL-cholesterol of 0.32 mmol/L by a low-intensity primary care-based intervention^10^. Attrition rates have been reported to be quite low in short term primary care-based trials^10 20^, so we could assume around 10% attrition rate in our study. In order to detect a reduction of 3% in %SFA intake (3% standard deviation) between each intervention and control with 90% power and two-sided α=0.05 using intention-to-treat analyses, we will need 16 participants in the control group and 48 in each intervention arm to account for 10% attrition and multiple comparisons. By recruiting 48 participants in each active intervention arms, we will be able to detect a further difference between these two arms of 2% (3% SD) with 90% power.

In addition, this sample size will allow to detect a change in LDL cholesterol of 0.3 mmol/L (SD 0.8) between each intervention and control with 60% power using a 2-sided α=0.05.

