## Analysis of Outcome Measures

As described above, primary and secondary outcomes which are continuous variables will be analysed using linear regression models in an ITT analysis as the primary statistical analysis.

The primary analysis will test for:

- A difference in the change (from baseline to follow up) in % SFA intake between each intervention group compared to control;

- A difference in the change (from baseline to follow up) in % SFA intake between the two active intervention arms.

Using the appropriate interaction terms in the above mentioned models, we will perform subgroup analyses of the primary and secondary outcomes by sociodemographic characteristics (SES), as a previous study has shown that lower SES households purchase a higher proportion of energy from less healthy foods with smaller but important differences in the SFA content from purchased foods which may lead to differential effectiveness^21^. While the study is not powered to look for such effects here, this information will inform planning of subsequent research.

Acceptability of the intervention by the participants will be collected by questionnaire and will be summarised by presenting the frequencies of each response in bar charts.

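### The sample size is said to allow for multiple comparisons, but it is the unadjusted 5% figure plus attrition, and the three primary tests each run at 5% with no named procedure

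*Protocol*

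**What the plan says.** Section 11.3 (Analysis of Outcome Measures) puts three tests of one outcome under the primary analysis. Two are the differences in change "between each intervention group compared to control". The third is "A difference in the change (from baseline to follow up) in % SFA intake between the two active intervention arms". No order or precondition links them.

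Section 11.1 (Description of Statistical Methods) sets the level: "All the tests will be done at a 5% two-sided significance level". Results are to be given as "comparative summary statistics (difference in means) with 95% confidence intervals".

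Section 11.2 (The Number of Participants) gives the target, "In order to detect a reduction of 3% in %SFA intake (3% standard deviation) between each intervention and control", to be met "with 90% power and two-sided α=0.05 using intention-to-treat analyses". It concludes that 16 control participants are needed and "48 in each intervention arm to account for 10% attrition and multiple comparisons". The same section adds that 48 per active arm gives 90% power for a 2-point difference between the active arms (SD 3).

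No adjusted level, testing sequence, global test or other multiplicity procedure appears in the protocol.

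**The concern.** Section 11.2 tells the reader that multiplicity has been dealt with, yet its own calculation and the testing rule in section 11.1 both use 5% throughout. If no allowance was made, the protocol claims a protection that it does not have, and the error rate over the family of primary tests is above the 5% that a reader would assume.

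This matters because the main hypothesis (section 4, Aims) concerns advice alone, or advice with the shopping report, or both, against usual care. Either control comparison could therefore be presented as support. The results are also meant to inform whether a definitive trial is planned.

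**Working it through.** **1. Reproduce the stated sample size.** Inputs from section 11.2: difference 3, SD 3, 90% power, two-sided α = 0.05, allocation 1:3 for control against each active arm, 10% attrition. With the normal approximation,

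n(control) = (1 + 1/3) × (SD/difference)² × (z(1−α/2) + z(0.90))²

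At α = 0.05: 1.3333 × 1 × (1.960 + 1.2816)² = 14.01. Dividing by 0.9 gives 15.6, so 16 control and 3 × 16 = 48 per active arm. This is the protocol's figure exactly, when rounding is left to the end. Rounding 14.01 up to 15 before adding attrition gives 17.

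**2. Repeat with a multiplicity allowance.**

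| Level per test | n(control) before attrition | After ÷ 0.9 | Approximate requirement |
|---|---|---|---|
| 0.05 (none) | 14.01 | 15.6 | 16 control, 48 per active arm |
| 0.025 (Bonferroni, two tests) | 16.55 | 18.4 | 19 control, 56–57 per active arm |
| 0.0167 (Bonferroni, three tests) | 18.01 | 20.0 | 20–22 control, 60–66 per active arm |

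The ranges reflect rounding. Neither adjusted level gives 16 and 48. The nearest approach is α = 0.025 with 16 and 48 and no attrition (88.9% power). With 10% attrition, which section 11.2 says is included, this falls to 85.2%.

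**3. Check the comparison between active arms.** For 2 points and SD 3 at α = 0.05: n per arm = 2 × (3/2)² × (1.960 + 1.2816)² = 4.5 × 10.51 = 47.3, so 48. Power with 48 per arm is 90.4%. With 10% attrition it is 87.3%. This figure contains no allowance for multiplicity, and none for attrition either.

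**4. Error rate of the rule as written.** The three contrasts are correlated. With 16/48/48 the two control comparisons have correlation 48/(48 + 16) = 0.75. The contrast between active arms has correlation (1/48)/√[(1/16 + 1/48)(1/48 + 1/48)] = 1/√8 = 0.35 in size with each of them. Simulation of the three contrasts with all arms equal, each tested at two-sided 5%, gives:

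| Family | 16/48/48 (4 million draws) | 14/43/43 evaluable, pooled variance |
|---|---|---|
| Any of the three primary tests | 11.9% | 11.8% |
| Either of the two control comparisons | 8.1% | 7.9% |
| Three tests behind a 2-df global test at 5% | not run | 5.0% |

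For reference, three independent tests would give 1 − 0.95³ = 14.3%, and the Bonferroni bound is 15%.

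**5. Cost of the global gate.** Simulated with 14/43/43 evaluable, SD 3 and pooled variance:

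- True reductions of 3 points in both active arms: power per control comparison falls from 89.5% to about 85%. Holm gives 81.7%.
- True reductions of 3 and 5 points: 89.5% and 99.9% against control, and 86.4% between the active arms. These are essentially the ungated values.

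**The case against.** **Testing order and gating often belong in the statistical analysis plan.** Section 11.1 promises a full plan before any analysis, and it is not available here. This stands as far as a missing procedure goes. It does not rescue section 11.2, which states as fact an allowance that its own inputs do not contain.

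**Sections 11.1 and 11.2 are not strictly incompatible.** A reader might infer that testing everything at 5% and controlling multiplicity cannot both hold. They can: behind a 5% global gate, every test is still at two-sided 5%. What is wrong is that no such procedure is named and that the sample size is credited with the allowance.

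**The 12% is not the risk of a false claim against usual care.** A reader might apply it to the main hypothesis. That hypothesis is worded against usual care, so its family is the two control comparisons and its rate is about 8%. The hypothesis is also directional. With all arms equal, the chance of at least one significant result favouring an intervention over control is about 4.0%. The 12% also counts apparent harm and differences in either direction between the active arms.

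**The link to a definitive trial is loose.** A reader might infer that one p-value below 0.05 triggers the next trial. The protocol says only that a definitive trial will be planned if results are promising. Section 14.5 calls this a feasibility study, and estimates with intervals are to be reported. That limits the consequence. Even so, section 4 aims to test effectiveness and section 11.2 powers the comparisons at 90%.

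**Separate interventions may need no adjustment.** That can be argued, but the protocol takes the opposite position by claiming an adjustment.

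**Conclusion.** The point holds in this form: the multiplicity allowance claimed in section 11.2 is absent from its calculation, and sections 11.1 and 11.3 run three primary tests at 5% each without a named procedure. The two-sided family-wise error is about 12% for the three primary tests and about 8% for the two comparisons with usual care.

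These rates assume that all three arms are truly equal, that variance is common, that allocation is 1:3:3, and that no gate or sequence is added elsewhere. They barely change with 10% attrition. The sample-size check rests only on the inputs in section 11.2 and the normal approximation.

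This should be fixed, but it does not undermine the design, because the error rate can be controlled without more participants.

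**What to change.** Name one procedure in sections 11.1 and 11.3. One option is to test the 2-df null of no difference among the three arms in the baseline-adjusted model at two-sided 5% and, only if it rejects, to test the three pairwise differences at 5% each. With exactly three arms this is a closed procedure that holds the family-wise error at 5%. A pre-specified fixed sequence would also do. The choice is the sponsor's.

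In section 11.2, delete the reference to multiple comparisons or tie it to the named procedure, and restate the power on evaluable numbers. Under the gate with 14/43/43, power per control comparison is about 85% if both arms have the 3-point effect, and about 90% or more if the effects are 3 and 5 points. For the 2-point comparison between active arms in that second case, it is about 86% rather than 90%.

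Report all three estimates with 95% intervals whatever the gate shows. State that these intervals are unadjusted, since one may exclude zero when the global test has not rejected. Label secondary outcomes as not controlled for multiplicity.

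The cost is a short amendment to three sections and up to about 5 points of power per control comparison. No extra participants are needed. Keeping 90% power under Bonferroni over three tests would instead need about 20–22 control and 60–66 per active arm for the control comparisons, and 68 per active arm for the 2-point comparison.

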## The Number of Participants

The total number of participants we intend to recruit for this study is 112, with a sampling ratio of 1:3:3. Therefore, 16 participants will be allocated to control, and 48 participants will be allocated to each of the two active interventions.

Previous studies such as highly controlled interventions in populations with high CVD risk have achieved absolute changes in %SFA intakes of around 4-5%^6 7^, and a short-term change in LDL-cholesterol of 0.32 mmol/L by a low-intensity primary care-based intervention^10^. Attrition rates have been reported to be quite low in short term primary care-based trials^10 20^, so we could assume around 10% attrition rate in our study. In order to detect a reduction of 3% in %SFA intake (3% standard deviation) between each intervention and control with 90% power and two-sided α=0.05 using intention-to-treat analyses, we will need 16 participants in the control group and 48 in each intervention arm to account for 10% attrition and multiple comparisons. By recruiting 48 participants in each active intervention arms, we will be able to detect a further difference between these two arms of 2% (3% SD) with 90% power.

In addition, this sample size will allow to detect a change in LDL cholesterol of 0.3 mmol/L (SD 0.8) between each intervention and control with 60% power using a 2-sided α=0.05.

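### The 16/48/48 sample size is said to allow for multiple comparisons, but it is the unadjusted single-comparison size plus 10% attrition

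*Protocol*

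**What the plan says.** Protocol Section 11.2 (The Number of Participants) sizes the trial on the change in %SFA intake. It aims to detect a difference of 3 percentage points, with an SD of 3, "between each intervention and control with 90% power". The level is given in the same sentence: "with 90% power and two-sided α=0.05 using intention-to-treat analyses". The total "we intend to recruit for this study is 112, with a sampling ratio of 1:3:3". On attrition it says "we could assume around 10% attrition rate in our study". It then concludes that "we will need 16 participants in the control group and 48 in each intervention arm to account for 10% attrition and multiple comparisons". No adjustment method and no adjusted alpha are named. For the two active arms it adds that "we will be able to detect a further difference between these two arms of 2% (3% SD) with 90% power".

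Section 11.1 (Description of Statistical Methods) says "All the tests will be done at a 5% two-sided significance level".

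Section 11.3 (Analysis of Outcome Measures) places three pairwise tests in the primary analysis: each intervention against control, and the two interventions against each other. It states no order of testing and no gatekeeping rule.

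**The concern.** Section 11.2 makes a factual claim about how the number was reached: that it covers both attrition and multiplicity. The alpha it quotes is an unadjusted 5%, and Section 11.1 applies 5% to every test. If the number already equals the unadjusted size plus attrition, the claim is untrue.

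At stake is the power statement for the primary outcome, on which ethics reviewers, the funder and readers of the trial report rely. Either the comparisons are tested without adjustment and multiplicity is not accounted for, or they are adjusted in a way that lowers the level of each test and the stated 90% is too high.

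**Working it through.** **Inputs (all from Section 11.2 unless noted).** Difference 3, SD 3; control to active 1:3; two-sided alpha 0.05; power 90%; attrition 10%. Active against active: difference 2, SD 3, 48 per arm. Primary comparisons: three (Section 11.3).

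**Reproducing the stated number.** For two means with 1:3 allocation,

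n(control) = (1 + 1/3) × (SD/difference)² × (z for alpha + z for power)²

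= (4/3) × 1 × (1.960 + 1.282)² = 14.01.

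Attrition: 14.01/0.9 = 15.57, rounded up to 16; 3 × 16 = 48; 16 + 48 + 48 = 112. The stated size is reproduced with no multiplicity term. (Rounding 14.01 up to 15 before inflating would give 17, so the stated number contains no hidden reserve.)

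**Size needed with a multiplicity allowance, same formula, 90% power, 10% attrition.** For Dunnett, two arms share one control, so the correlation between the two tests is 48/(16 + 48) = 0.75. The critical value is 2.168, a per-test alpha of 0.0302.

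| Adjustment | Alpha per test | n(control) | ÷ 0.9 | Arms at 1:3:3 | Total |
|---|---|---|---|---|---|
| None | 0.05 | 14.01 | 15.57 | 16:48:48 | 112 |
| Dunnett, two control comparisons | 0.0302 | 15.86 | 17.6 | 18:54:54 | 126 |
| Bonferroni, two | 0.025 | 16.55 | 18.4 | 19:57:57 | 133 |
| Bonferroni, three | 0.0167 | 18.01 | 20.01 | 21:63:63 | 147 |

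The last row rounds 20.01 up; 20 controls would be almost enough.

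**Power of the stated size, each intervention against control, after 10% attrition** (16 × 0.9 = 14.4 and 48 × 0.9 = 43.2). The t-based column uses the noncentral t with two-arm degrees of freedom.

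| Adjustment | Normal approximation | t-based |
|---|---|---|
| None | 90.8% | 89.8% |
| Dunnett | 86.8% | 85.3% |
| Bonferroni, two | 85.2% | 83.4% |
| Bonferroni, three | 81.4% | 79.0% |

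With whole completers (14 and 43), the t-based figures for no adjustment, Bonferroni over two and Bonferroni over three are 89.1%, 82.5% and 78.0%.

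**Active against active.** n per arm = 2 × (3/2)² × (1.960 + 1.282)² = 47.3, rounded up to 48. This is the unadjusted size before any attrition. At 43.2 per arm, power (normal approximation) is 87.3% unadjusted, 80.4% at alpha 0.025 and 75.9% at alpha 0.0167.

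**Familywise error if every test is run at 5%.** Simulated with the trial's shared arms and no true effect: about 8% for the two control comparisons and about 12% for all three.

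**The case against.** The best defence is that Section 11.2 names alpha 0.05 and Section 11.1 applies 5% to every test. At that level, 90% per control comparison is correct, so the number, alpha, effect and SD agree with one another. On this view the fault is a few unsupported words. That is a fair account of where the error lies, but those words state a property that the design lacks.

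The shortfall also depends on a method the Protocol does not name:

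- A fixed sequence would leave the first comparison at its full 5% power.
- With exactly three groups, a global two-degree-of-freedom test followed by 5% pairwise tests controls familywise error at 5%. Simulated at 14/43/43, power for an effective arm is about 89% when only one arm works and 85% when both do.
- Holm over the two control comparisons gives 87% when both arms work.
- Pooling the error variance over all three arms raises the t-based figures slightly: 90.2% unadjusted, 86.0% with Dunnett, and 84.2% and 80.1% with Bonferroni over two and three.

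All of this stands as to size. None of it makes the sentence true, because the text says the allowance is in the number of participants, and a procedure that needs no extra participants is not what that number accounts for.

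The planned baseline adjustment could recover power. If the SD of 3 is the raw follow-up SD, which the Protocol does not say, a correlation of 0.36 between baseline and follow-up would restore 90% under Bonferroni over two tests, and 0.45 over three. The Protocol gives no correlation and claims no such gain.

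Finally, 16/48 does reach 90.3% (normal approximation) under Dunnett if nobody is lost. It can cover attrition or a Dunnett adjustment, but the text claims both.

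**Conclusion.** The concern holds. The stated size contains an allowance for 10% attrition and none for multiple comparisons, so the sentence in Section 11.2 is wrong as written. Against the stated 90%, power for each control comparison is about 5 points lower under Dunnett and 7 to 12 points lower under Bonferroni (t-based, over two or three tests, at 14.4/43.2 or 14/43 completers). On the normal approximation the gaps are 3 points for Dunnett and 5 to 9 for Bonferroni. A closed test or fixed sequence would lose less. These figures assume the Protocol's own difference of 3, SD of 3 and 10% attrition, with no gain from baseline adjustment. The active-against-active claim has less room still, because its 48 per arm does not cover attrition either.

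**What to change.** In Section 11.2, delete the reference to multiple comparisons. State that 16/48/48 gives about 90% power for each control comparison at an unadjusted two-sided 5% level after 10% attrition.

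Deletion alone would leave three primary tests with no stated position on multiplicity. So also name the procedure to be used, reconcile it with the blanket 5% level in Section 11.1, and give the power under it: about 85% with Dunnett, 83% with Bonferroni over two tests, 79% with Bonferroni over three, or 85% to 90% with a global test followed by 5% pairwise tests. If the three tests are to remain unadjusted, say so and acknowledge the familywise error of about 12%. In the same edit, correct the active-against-active figure to about 87% after attrition at an unadjusted 5%.

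The cost is wording and a slightly less favourable stated power. No extra participants are needed unless the team wants to keep 90% under an adjusted level, which would take the total from 112 to between 126 and 147 for the control comparisons.

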Building on what is known but bearing in mind scalability, we propose to develop and test a novel intervention to decrease SFA intake. In one group, a brief advice session will provide motivational force using a qualified health professional to explain the importance of SFA intake and the impact this could make to a patient’s cholesterol. But recognising that health professionals may lack sufficient time and training to go beyond general messages about how to reduce SFA, we propose another intervention to provide personalised feedback and self-monitoring of dietary habits, which has further potential to achieve and sustain behaviour change^14^. Therefore, a second group will receive a brief advice session in combination with a personalised report on purchasing behaviours (provided monthly over the 3 months of follow up), to enhance the participants capability to make dietary changes when shopping for food. By drawing on the power of data already collected by supermarkets we are able to automate the process which would otherwise require considerable time from dietitians to deliver. These two groups will be compared to a control group which will just receive their blood test results without any further advice.

We will enrol people with raised LDL cholesterol who are willing to try to change their diet, perhaps to avoid the need for long-term medication. At this stage we will examine the effect of the intervention on saturated fat intake as the primary outcome and, if promising, we will plan for a definitive trial to test the effectiveness of the intervention to reduce LDL cholesterol. This proposed intervention is low cost and could reach large numbers, meaning that it could have a significant population impact and be very cost-effective, even if the effect size is smaller than more intensive interventions. If successful, similar interventions could be offered by supermarkets to all their customers to bring health benefits to the whole population and encouraging supermarkets to play a more proactive role in shaping healthier choices for their customers.

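### The stated 60% power for LDL cholesterol does not follow from its own inputs: 16 versus 48 gives about 25%, or 22–23% after the planned attrition

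*Protocol*

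**What the plan says.** Section 11.2 gives the arm sizes: "16 participants will be allocated to control, and 48 participants will be allocated to each of the two active interventions". On attrition it reasons from earlier trials, "so we could assume around 10% attrition rate in our study". After the two power statements for saturated fat intake, it adds that the same sample size will detect "a change in LDL cholesterol of 0.3 mmol/L (SD 0.8) between each intervention and control with 60% power", with a two-sided α of 0.05. Section 11.1 confirms the level: "All the tests will be done at a 5% two-sided significance level".

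The section does not say whether 0.8 is the SD of the LDL level, of its change, or the residual SD after adjustment. It gives no baseline to follow-up correlation. Section 11.1 plans to analyse secondary outcomes by linear regression adjusted for practice and baseline value.

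LDL cholesterol is a secondary outcome. The Background says of the next step: "if promising, we will plan for a definitive trial to test the effectiveness of the intervention to reduce LDL cholesterol".

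**The concern.** The sentence supplies everything needed to check it: difference, SD, significance level, comparison and arm sizes. A standardised difference of 0.3/0.8 = 0.375 is modest, and the comparison is limited by a control arm of 16. Power of 60% looks far too high for that combination.

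At stake is how the LDL result will be read. LDL is the outcome that links this trial to the proposed definitive one. A reader who believes the trial had 60% power would treat a non-significant LDL difference as moderately informative. If power is nearer 25%, such a result says very little. The figure could also be carried into the planning of the next trial.

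**Working it through.** **Inputs (Protocol 11.1 and 11.2).** Difference 0.3 mmol/L; SD 0.8 mmol/L; control n = 16; each intervention n = 48; two-sided α = 0.05; attrition 10%.

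**Method.** Two-sample comparison of means. The standard error is SE = SD × √(1/n₁ + 1/n₂), the noncentrality is δ/SE, and power comes from the noncentral t distribution with n₁ + n₂ − 2 degrees of freedom.

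**Does the method reproduce the protocol's other power figures?** For saturated fat, each intervention against control (difference 3, SD 3, stated power 90%), it gives 92.6% at 16 versus 48 and 89.1% at 14 versus 43. For the two active arms (difference 2, SD 3, stated power 90%), it gives 89.8% at 48 versus 48. Both agree with the protocol to within rounding, with no baseline adjustment and α = 0.05.

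**LDL, as stated.**
- SE = 0.8 × √(1/16 + 1/48) = 0.8 × √0.08333 = 0.231
- Noncentrality = 0.3 / 0.231 = 1.30
- Power = **24.9%** (about 25.5% by the normal approximation), against 60% stated

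**LDL, after 10% attrition** (16 × 0.9 = 14.4; 48 × 0.9 = 43.2).
- 14.4 versus 43.2: SE = 0.243, noncentrality 1.23, power **22.8%**
- 14 versus 43: SE = 0.246, noncentrality 1.22, power **22.4%**

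**Could another reading give 60%?** All rows are unadjusted.

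| Reading | Power |
| --- | --- |
| One-sided test, 16 vs 48 | 35.9% |
| Difference of 0.32 (the LDL change cited in 11.2), 16 vs 48, normal approximation | 28.3% |
| Both interventions pooled against control, 16 vs 96 | 28.0% |
| The two active arms against each other, 48 vs 48 | 44.4% |

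None reaches 60%, and the last is not an intervention-versus-control comparison.

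**What would give 60%?**
- A difference of 0.52 mmol/L at 16 versus 48, or 0.55 mmol/L at 14 versus 43, with SD 0.8; or
- an effective SD of 0.46 at 16 versus 48, or 0.43 at 14 versus 43, with difference 0.3; or
- about 47 controls and 141 per intervention arm, with difference 0.3 and SD 0.8.

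Entering 48 as the smaller arm at a 1:3 ratio (48 versus 144) gives 61%. That may be where the figure came from, but this is a guess and nothing here depends on it.

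**Effect of baseline adjustment.** If 0.8 is the SD of the LDL level and r is the baseline to follow-up correlation, the residual SD is 0.8 × √(1 − r²). The protocol gives no r, so the values below are assumptions.

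| r (assumed) | Residual SD | Power, 16 vs 48 | Power, 14 vs 43 |
| --- | --- | --- | --- |
| 0.5 | 0.69 | 31% | 28% |
| 0.7 | 0.57 | 43% | 39% |
| 0.8 | 0.48 | 57% | 51% |
| 0.85 | 0.42 | 68% | 62% |

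Power of exactly 60% needs r = √(1 − (0.46/0.8)²) ≈ 0.82 at 16 versus 48, and about 0.84 at 14 versus 43.

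**The case against.** The strongest objection is that 25% describes an unadjusted comparison, while the planned model adjusts for baseline. If 0.8 is the SD of the LDL level, the planned analysis has more power than 25%, and at a correlation a little above 0.8 it has 60%. This stands in part: 25% cannot be called the power of the planned analysis until the meaning of the SD is settled.

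It does not rescue the sentence. Section 11.2 gives the SD as 0.8 and mentions no correlation or variance reduction. The two saturated fat figures in the same section are reproduced without any adjustment, so nothing indicates that LDL alone was treated differently. If 0.8 is already the SD of change (analysed as a change) or the residual SD, 25% stands.

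A second objection concerns importance. LDL is secondary, the sentence does not set the sample size, and 60% is itself openly below the 90% claimed for saturated fat. The Background makes saturated fat intake the outcome for this stage and does not tie the decision on a definitive trial to an LDL test. Section 11.1 already commits to mean differences with 95% confidence intervals. All of this is fair. It limits the consequences of the error but does not make the figure right.

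**Conclusion.** The stated 60% is not supported by the inputs printed beside it. Those inputs give 24.9% power, and 22.4% to 22.8% after the protocol's 10% attrition, so the stated figure is more than twice what they yield. A true 0.3 mmol/L effect would go undetected about 75% of the time (77% to 78% after attrition), not 40%.

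This rests on reading 0.8 as the SD that applies to the comparison. If it is the SD of the LDL level and baseline adjustment was intended, power lies between about 28% and 57% for assumed correlations of 0.5 to 0.8, across both attrition cases. It reaches 60% only at about 0.82 without attrition or 0.84 with it. The primary outcome's sample size is not affected.

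**What to change.** First establish what the 0.8 represents and whether a baseline correlation was assumed.

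- If none was assumed, replace the LDL sentence in section 11.2 with wording such as: *For LDL cholesterol, this sample size gives about 25% power (about 23% after 10% attrition) to detect a difference of 0.3 mmol/L (SD 0.8) between each intervention and control at two-sided α = 0.05; a difference of about 0.5 mmol/L would be detectable with 60% power.*
- If one was assumed, state the correlation, its source and the residual SD, and recalculate the power at the numbers expected after attrition.

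It would also help, though it is optional, to add that the LDL result will be read from its estimate and 95% confidence interval, and that a non-significant difference will not be taken as evidence of no effect.

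The cost is one corrected sentence and a less favourable figure. Arm sizes, analysis and conduct do not change.
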